## 5.2 - Missed Next visit

**Outcome:** This secondary outcome for retention will be whether an individual misses their next visit by more than 30 days. We will use EHR data (i.e., SmartCare) that includes sociodemographic, clinical, visit history, and pharmacy data to determine this outcome. These complement 15th month assessments because are able to consider shorter term effects of the intervention rather than a single endpoint at 15 months which reflect the cumulative effects over all observation time until that time point.

**Population:** The population for this outcome will include all individuals ( $\geq 18$  years old) who made a visit to one of our study clinics during the 6 months prior to our study and period through to the end of the 24-month study period. This analysis will include individuals from facilities in all waves.

|        | Period 0                                                   | Period 1                                                        | Period 2                                                        | Period 3                                                        | Period 4                                                        | Totals per wave |
|--------|------------------------------------------------------------|-----------------------------------------------------------------|-----------------------------------------------------------------|-----------------------------------------------------------------|-----------------------------------------------------------------|-----------------|
| Wave 1 | Control
All Visits made during Period
~60,000 | Intervention
All Visits made during Period
~60,000 | Intervention
All Visits made during Period
~60,000 | Intervention
All Visits made during Period
~60,000 | Intervention
All Visits made during Period
~60,000 | ~300,000 visits |
| Wave 2 | Control
All Visits made during Period
~30,000 | Control
All Visits made during Period
~30,000      | Intervention
All Visits made during Period
~30,000 | Intervention
All Visits made during Period
~30,000 | Intervention
All Visits made during Period
~30,000 | ~150,000 visits |
| Wave 3 | Control
All Visits made during Period
~30,000 | Control
All Visits made during Period
~30,000      | Control
All Visits made during Period
~30,000      | Intervention
All Visits made during Period
~30,000 | Intervention
All Visits made during Period
~30,000 | ~150,000 visits |

| Wave 4               | Control
All Visits made
during Period
~60,000 | Control
All Visits made
during Period
~60,000 | Control
All Visits made
during Period
~60,000 | Control
All Visits made
during Period
~60,000 | Intervention
All Visits made
during Period
~60,000 | ~300,000 visits |
|----------------------|---------------------------------------------------------------|---------------------------------------------------------------|---------------------------------------------------------------|---------------------------------------------------------------|--------------------------------------------------------------------|-----------------|
| Totals per
period | 180,000 visits                                                | 180,000 visits                                                | 180,000 visits                                                | 180,000 visits                                                | 180,000 visits                                                     | ~900,000 visits |

Analysis: This analysis will include data from all studies leveraging the full stepped-wedge design. The 6-month period prior to study start will be included as a Period 0 when all facilities are control. We will use mixed effects logistic regression, accounting for clustering at both the individual- and the facility-level using random effects. The main exposure will be exposure to the PCC intervention and will be assigned at the visit level. As some individuals may be seen more than once during the study period and cross-over from control to intervention, each visit will be categorized as control or intervention based on when it occurred (e.g., an individual may have one visit assigned as control and a later visit categorized as intervention). Due to a potential lag in intervention effect, we will code intervention periods as control, early intervention ( $\leq 6$  months), and late intervention ( $> 6$  months) (Hughes et al., 2015; Kenny et al., 2021). To account for potential imbalances due to cluster randomization at baseline and also increase precision, we will adjust for individuals' care status at enrollment (in care, new ART, LTFU), sex, age, time in care, baseline clinic-level retention (i.e., percent of visits where patient was more than 30 days late to their next appointment assessed in the 6 months prior to study start), and randomization strata (initial cluster randomization stratified by facility size and viral load coverage based on programmatic data). Facility will be included as a random effect. We will consider including the following potential confounders due to imbalance in randomization: WHO severity groups, marital status, and education. We will use standard model diagnostic procedures and consider alternate specifications as needed if we face challenges with standard statistical issues such as model convergence or overfitting. We will use marginal estimation commands to report absolute and relative risk differences under treatment versus control conditions.

In addition to the overall analysis, we will perform stratified analyses to assess changes specifically across:

- Care Status at time of visit (in care, new ART, LTFU)
- Sex
- Age (<25, 25-44, >45)
- Advanced HIV Disease at enrollment in care (WHO Stage 3 or 4, CD4<200) – Dependent on adequate coverage of CD4 measurements
- Clinic Size and Type
- We may assess composite subgroups of age, sex, and care status (e.g., Male <25 years old, LTFU not suppressed at baseline) if amenable based on sample sizes. We will not perform analyses with less than 500 participants.

Sensitivity Analysis: We will perform several sensitivity analyses to ensure the robustness of our results by considering 90 days late threshold instead of 30 for the outcome. We will also explore alternate specifications for the intervention variable where we assume the maximal intervention effect will be quicker (i.e., 3 months) or longer (i.e., 9 months).

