|                                                                                                                             | N         | N (%)                  | N (%)                           | N (%)                           | Risk Difference
(95% CI)     | p-value | Risk Difference
(95% CI)     | p-value |
| Overall                                                                                                              | 1,009,352 | 130,035 (22.1)         | 40,380 (22.6)                   | 52,288 (21.5)                   | -2.0
(-2.3 – -1.7)           | <0.001  | -3.7
(-4.1 – -3.4)           | <0.001  |
| Baseline
Care
Status                                                                                  |           |                        |                                 |                                 |                                 |         |                                 |         |
| New
ART                                                                                                                  | 54,391    | 8,318 (28.5)           | 3,219 (31.9)                    | 4,323 (28.6)                    | -1.2
(-2.5 – 0.2)            | 0.095   | -4.7
(-6.6 – -2.9)           | <0.001  |
| In Care                                                                                                                     | 805,353   | 99,808 (20.5)          | 28,635 (20.5)                   | 33,305 (18.8)                   | -2.0
(-2.4 – -1.7)           | <0.001  | -3.4
(-3.9 – -3.0)           | <0.001  |
| Returner                                                                                                                    | 149,608   | 21,[name] (31.2)          | 8,526 (29.6)                    | 14,660 (29.0)                   | -0.6
(-1.6 – 0.3)            | 0.20    | -2.0
(-3.4 – -0.7)           | 0.004   |
| Sex                                                                                                           |           |                        |                                 |                                 |                                 |         |                                 |         |

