### Study design:

We used a stepped wedge cluster randomised trial to assess the effect of the PCC intervention in 24 clinics. We introduced the intervention at four randomly-determined time points at study start, 6, 12 and 18 months. We followed all sites for a total of 24 months. The size of each sequence was not the same, with eight facilities in sequence 1, four in sequence 2, four in sequence 3 and eight in sequence four. The unequal weights allow us to power outcomes such as viral load that occur over periods of time that are longer than each period, and for which cross over would preclude comparison of each treatment condition.

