#### Analysis

The analytic strategy for TEC will be focused on assessing the effectiveness of the PCC intervention by comparing the PCC intervention group to the control group. The unit of randomization is healthcare facility and the unit of analysis is the individual. To test the effectiveness of the

intervention, we will use a standard stepped-wedge analytic approach (Hussey & Hughes, 2007) based on a generalized linear mixed model (GLMM) where facility is included as a random effect and period is included as a fixed categorical variable to adjust for secular trends. Due to a ramp up in intervention effect, we will determine code three different groups for the intervention analysis (control, early intervention ( $\leq 6$  months), late intervention ( $> 6$  months), fit as separate categories or ordered (Hughes et al., 2015; Kenny et al., 2021)). This decision is based on contextual experience in the facilities and anticipation that there will be a lag in seeing the benefits from training, mentoring, and data feedback (e.g., the first data feedback only occurred 3 months into the intervention). Furthermore, we will explore alternative parameterizations for secular trends including linear and cubic splines. If these alternative parameterizations better describe variability in the data (as determined by standard model fit statistics such as Akaike's Information Criterion [AIC]) then the model will be updated to reflect this accordingly. Distributions and link functions used will depend on the outcome (see outcome-specific sections below for more details).

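### SAP 5.2 omits any facility-by-period variation from the missed-visit model, so its confidence intervals are too narrow, by a factor that depends on a variance the documents do not give

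*Combined protocol and SAP*

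**What the plan says.** SAP section 5.2 (Missed Next visit) analyses every visit in all 24 facilities over Periods 0 to 4, about "900,000 visits" in total. The model is a mixed-effects logistic regression "accounting for clustering at both the individual- and the facility-level using random effects", and a later sentence repeats "Facility will be included as a random effect". Exposure is assigned per visit: "we will code intervention periods as control, early intervention" (up to 6 months) and late intervention (beyond 6 months). The list of adjustment variables does not name a period term.

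SAP section 4.0 (trained exit client survey, TEC) uses a Hussey-Hughes model in which "facility is included as a random effect and period is included as a fixed categorical variable to adjust for secular trends".

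Neither section has a facility-by-period random effect, a cluster-robust variance or a small-sample correction. In 5.2, departures from the stated model are allowed only for problems such as convergence or overfitting. The sensitivity analyses in 5.2 change only the lateness threshold (90 days) and the assumed lag (3 or 9 months). No intraclass or between-period correlation is given for missed visits.

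**The concern.** A facility intercept lets facilities differ in level. Without a facility-by-period term, the model assumes that, apart from the intervention, all facilities move in parallel over time. The individual intercept does not relax this, because a shock shared by one facility's patients in one period is not a property of any single patient. A logistic model also has no free residual variance in which such shocks could show up.

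The protocol itself expects local shocks. Under Objective 1 and section 6.0 it plans to track workforce vacancies, power supply, drug supplies and staffing levels because they can affect delivery. With thousands of visits per facility and period, sampling noise is so small that modest drift of this kind dominates the real error of a stepped-wedge contrast.

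At stake are the interval widths and p-values for the missed-visit effects in Supplemental Appendix Tables S8 and S13. This is the only retention outcome that uses all 24 facilities.

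**Working it through.** **Inputs from the documents.** Facilities: "eight facilities in sequence 1, four in sequence 2, four in sequence 3 and eight in sequence four" (SAP, Study design). Visits: 900,000 / (24 x 5) = 7,500 per facility-period; the 5.2 table gives the same in every cell (60,000/8 = 30,000/4 = 7,500). Rate: 22% (Table S13, control 22.1%). Reported effects in Table S13: early -2.0 (-2.3 to -1.7), late -3.7 (-4.1 to -3.4).

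**Assumed.** Facility SD 6 points, which is an ICC of 0.06² / (0.22 x 0.78) = 0.021. Facility-by-period SD, called s, of 0.25 to 4 points. Periods of equal length, categorical period, no covariates, linear scale, individual effect left out.

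**Step 1, noise per cell.** 100 x sqrt(0.22 x 0.78 / 7,500) = 0.478 points; variance 0.229.

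**Step 2, reproduce the reported precision.** Generalised least squares on facility-period means, with period indicators plus early and late terms. The covariance V has 36 shared within a facility plus 0.229 per cell, and Var(b) = (X'V⁻¹X)⁻¹. The 95% half-widths are:
- Periods 0-4: 0.31 early and 0.43 late. At the analysed number of visits (1,009,352/120 = 8,411 per cell) they are 0.29 and 0.41. Table S13 reports (2.3 - 1.7)/2 = 0.30 and (4.1 - 3.4)/2 = 0.35.
- Periods 1-4: 0.36 and 0.56. Table S8 reports (2.5 - 1.7)/2 = 0.40 and (4.8 - 3.7)/2 = 0.55.

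**Step 3, allow facility-by-period variation.** The true covariance is V + s²I. The sandwich variance of the planned estimator gives the true half-width. The ratio to the planned half-width is very close to sqrt(1 + s²/0.229); for s = 1 this is sqrt(5.37) = 2.32. Type I error = 2[1 - Φ(1.96/ratio)]. The intervals below are centred on the Table S13 estimates, with half-widths from 7,500 visits per cell.

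| s (points) | Ratio | True half-width, early / late | Type I error | Early, 95% | Late, 95% |
|---|---|---|---|---|---|
| 0.25 | 1.1 | 0.35 / 0.49 | 8% | -2.35 to -1.65 | -4.19 to -3.21 |
| 0.5 | 1.4 | 0.45 / 0.62 | 18% | -2.45 to -1.55 | -4.32 to -3.08 |
| 1 | 2.3 | 0.72 / 1.00 | 40% | -2.72 to -1.28 | -4.70 to -2.70 |
| 2 | 4.3 | 1.34 / 1.85 | 65% | -3.34 to -0.66 | -5.55 to -1.85 |
| 3 | 6.4 | 1.98 / 2.73 | 76% | -3.98 to -0.02 | -6.43 to -0.97 |
| 4 | 8.4 | 2.62 / 3.62 | 82% | -4.62 to 0.62 | -7.32 to -0.08 |

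These use the normal multiplier 1.96. With a t multiplier of 2.07 (22 df, taken for illustration), the late half-width at s = 4 becomes 3.62 x 2.07/1.96 = 3.82, which passes 3.7. In the Period 1-4 analysis of Table S8 (late -4.2), the late half-width at s = 4 is 0.56 x 8.4 = 4.7, so there the late effect would also reach zero.

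**Step 4, a partial anchor in the documents.** Retention compares 8 with 8 facilities (Table S8: 5.9, 0.6 to 11.2). The half-width is 5.3, so SE = 5.3/1.96 = 2.70. If facility variation dominates, SE² = 2 x SD²/8, so SD = 2 x 2.70 = 5.4 points. On the missed-visit scale this is an ICC of 0.054²/0.1716 = 0.017, near 0.02. At ICC 0.02, a between-period correlation of 0.99 widens the Table S13 intervals 1.6 times, 0.95 widens them 3.1 times and 0.80 widens them 5.7 times. The correlation itself is not in the documents.

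**Step 5, TEC.** Cells hold 15 to 30 patients (SAP 4.0 table). At 15 and a 22% rate the noise is 100 x sqrt(0.1716/15) = 10.7 points, so even s = 4 gives sqrt(1 + 16/114.4) = 1.07. At 30 per cell it gives sqrt(1 + 16/57.2) = 1.13. The full calculation with the planned cell sizes gives 1.07 to 1.08.

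**The case against.** The best defence is that the size is unknown. The documents quantify no facility-by-period variation, and at an SD of 0.25 points the intervals would be only 1.1 times too narrow. That stands, and it is why the result is shown as a range.

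The main COVID-19 shock was also largely common. The dispensing directive covered all patients and all sites, and categorical period terms would absorb a shared shock. This stands in part: section 5.2 does not name such terms, and staffing, stock and power problems are local. The extra mentor visits in Groups 1 and 2 (Figure S4) came through the study's own mentors, so they are not clean evidence of independent drift.

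The agreement with Table S13 is suggestive, not proof of the model that was fitted: the late half-width is 0.43 (or 0.41) computed against 0.35 reported.

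For TEC, SAP 4.0 plans period-stratified and facility-stratified analyses, and protocol section 8.1.2 describes combining period-specific estimates. Within-period comparisons do not need facilities to move in parallel. That weakens the case for TEC but does nothing for section 5.2.

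Finally, missed visits is a secondary outcome. The primary outcome and 15-month retention compare waves 1 and 4 in parallel and are not affected.

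**Conclusion.** The omission is real, nothing else in the plan makes up for it, and it can only make the missed-visit intervals too narrow. How much depends on the assumed facility-by-period SD: from 1.1 times at 0.25 points to 8.4 times at 4 points. Already at 0.5 points the nominal 5% test has about 18% error.

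Four stronger readings are tempting and are not supported:
- That the intervals are several-fold too narrow as a matter of fact. This needs an SD of roughly 1 point or more, which no document states.
- That the p<0.001 results merely reflect the visit count. In the Period 0-4 analysis with the normal multiplier, at an SD of 2 points the late effect still has z = 1.96 x 3.7/1.85 = 3.9 and the early effect z = 1.96 x 2.0/1.34 = 2.9. The early effect becomes borderline at about 3 points; the late effect excludes zero throughout the range, though at 4 points so narrowly that a small-sample multiplier could remove it.
- That the model has a facility intercept alone. Section 5.2 also has an individual intercept, although it does not help here.
- That TEC is comparably affected. Its inflation is about 1.1 times at most over this range.

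The plan's stated certainty is what fails, not necessarily the direction of the result. The calculation is a linear approximation with equal cells.

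**What to change.** In SAP 5.2, add a facility-by-period random intercept, or use a facility-level cluster-robust variance. Either way, apply a small-sample correction suited to 24 facilities. State the categorical period term explicitly in the model. Report the estimated facility-by-period variance, so that readers can see where in the range above the trial falls. A permutation test that re-assigns facilities to sequences within randomisation strata is an optional check.

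The cost is SAP wording, a re-run and wider confidence intervals; no new data are needed. The same term may be added to SAP 4.0 for consistency, but it will change little there.

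### SAP 5.2 lists no calendar-period term and pools all exposure beyond 6 months; once period effects are added, the late term is not an average of the effects after month 6

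*Combined protocol and SAP*

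**What the plan says.** SAP 5.2 (Missed Next visit, Analysis): "Due to a potential lag in intervention effect, we will code intervention periods as control, early intervention" and late intervention, split at 6 months. The section calls for the full stepped-wedge design, with random effects for individual and facility. The listed adjusters are care status, sex, age, time in care, baseline clinic retention and randomization strata. Calendar period is not among them. On the baseline, the section says: "The 6-month period prior to study start will be included as a Period 0 when all facilities are control".

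SAP 4.0 (Patient Experience, Analysis) uses the same split for TEC: "Due to a ramp up in intervention effect, we will determine code three different groups for the intervention analysis". That section does include period, as a categorical fixed effect.

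The layout comes from the SAP's Study design paragraph: "We introduced the intervention at four randomly-determined time points at study start, 6, 12 and 18 months", with "eight facilities in sequence 1, four in sequence 2, four in sequence 3 and eight in sequence four". Wave 1 therefore accrues up to 24 months of exposure as planned. Figure S1 shows periods of 6, 9, 6 and 6 months as delivered, which makes it 27.

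The check on the coding in 5.2 is to move the cut: "We will also explore alternate specifications for the intervention variable where we assume the maximal intervention effect will be quicker" (3 months) or slower (9 months). The footnote to Table S13 moves the Period 0 analysis to the supplement, so the main missed-visit analysis is the one without Period 0.

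**The concern.** A single late term assumes that the effect is constant from month 6 on. In a stepped wedge with period effects, clinics that have long been exposed help to estimate the period effects against which later-crossing clinics are judged. If the effect keeps changing after month 6, the late coefficient is then a weighted sum whose weights need not be positive, and it need not lie between the smallest and largest true late effects.

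Leaving the period effects out avoids this but leaves calendar change in the estimate. That matters here: the legend to Figure S6 says appointment intervals lengthened greatly during the pandemic, and protocol section 5.1 (Objective 1) records a directive for 6-month dispensing.

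A non-flat effect is plausible in either direction. The SAP expects a ramp-up, the Intervention Description says meeting facilitation passed gradually to facility staff, and the Figure S4 legend reports more mentor visits in Groups 1 and 2. At stake is the reading of the greater-than-6-month effect on two secondary outcomes.

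**Working it through.** **Layout check.** The 5.2 table has 5 periods x (60,000 + 30,000 + 30,000 + 60,000) = 900,000 visits, the SAP's total. Per clinic-period this is 60,000/8 = 30,000/4 = 7,500. The TEC periods sum to 300 + 300 + 360 + 240 = 1,200, as stated.

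**Model.** For clinic i in period j: mean outcome = period effect + early term + late term + clinic effect + error. With total variance T, ICC r, cluster autocorrelation a and cell size n:
- covariance between two periods of one clinic = T·r·a;
- variance of a clinic-period mean = T·r + T(1 - r)/n.

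The generalized least squares estimator is (X'V⁻¹X)⁻¹X'V⁻¹Y. The weight on an exposure band is the sum of the late-term row over the clinic-periods in that band. T cancels from the weights. The SAP gives ICC 0.2 for TEC and none for 5.2, so for 5.2 r = 0.001-0.2 and a = 0.5-1 are assumed.

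**Late-term weights, SAP 5.2, planned layout** (r = 0.05, a = 1)

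| Model | 6-12 m | 12-18 m | 18-24 m |
|---|---|---|---|
| Period effects, with Period 0 | 0.97 | 0.25 | -0.22 |
| Range over assumed r and a | 0.81 to 0.97 | 0.25 to 0.28 | -0.09 to -0.23 |
| Period effects, no Period 0 | 1.41 | 0.18 | -0.59 |
| As written: no period term, with Period 0 | 0.51 | 0.32 | 0.18 |

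**Delivered layout (6/9/6/6 months), period effects, r = 0.05, a = 1**

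| Model | 6-12 m | 12-18 m | 18-21 m | 21-27 m |
|---|---|---|---|---|
| With Period 0 | 0.82 | 0.31 | 0.08 | -0.22 |
| No Period 0 | 1.18 | 0.31 | 0.03 | -0.51 |

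Each row sums to 1 within rounding, so an effect that is flat after month 6 is recovered without bias. A logistic fit to expected cell probabilities on the planned layout with Period 0 gives 1.00 / 0.26 / -0.26, in agreement. The early term also picks up later exposure: +0.29, -0.03 and -0.27 on the three later bands (planned, Period 0).

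**Size, by hypothetical example** (percentage points; planned layout with Period 0; effects in months 0-6, 6-12, 12-18, 18-24)
- Fading, -2, -4, -2, 0: late estimate = 0.97(-4) + 0.25(-2) - 0.22(0) = -4.4. The mean over months 6-18, where control clinics remain, is (-4 - 2)/2 = -3.0. Over all late months it is -2.0.
- Growing, -2, -4, -6, -8: late estimate = 0.97(-4) + 0.25(-6) - 0.22(-8) = -3.6. The mean over months 6-18 is -5.0; over all late months it is -6.0.

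Against the months with concurrent controls, the error is about 1.4 points in each example.

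**Moving the cut.** On the delivered layout, months 21-27 still carry about -0.24 (3-month cut) and -0.15 (9-month cut) with Period 0, and about -0.44 and -0.47 without it.

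**TEC** (Waves 2-4, SAP cell sizes, a = 1). Late-term weights on months 6-12 / 12-18 are 1.01 / -0.01 at ICC 0.2, 0.94 / 0.06 at 0.05, and 0.84 / 0.16 at 0.01.

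**The case against.** Several points against the concern stand.

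- A reader might infer that both stepped-wedge models weight the longest exposure negatively. They do not. In TEC that weight is about zero or positive, and exposure beyond 12 months occurs only in Wave 2, Period 4 (60 patients), when no control clinic remains. Little weight there is reasonable; what needs correcting is the label.
- The negative weight in 5.2 depends on period effects that the section does not list. As written, every late weight is positive. The SAP's reliance on the full stepped wedge suggests that period terms were intended, but it does not say so.
- A plateau after month 6 fits the SAP's lag rationale and gives no bias. The fading and growing paths above are illustrations, not evidence.
- A reader might infer that the reported late missed-visit effect of -4.2 points (Table S8) is wrong. The documents do not support that. Adding Period 0 gives -3.7 (Table S13). The difference of 0.5 is in the direction that fading would produce. For a fading effect of -4, -2, 0, 0 on the delivered layout, the late estimate is -3.9 with Period 0 and -5.3 without, a difference of 1.4. The reported shift is about a third of that, and other explanations are open.
- TEC has more safeguards than 5.2: separate or ordered coding, alternative time trends, and period-stratified analyses that compare clinics within a period. In 5.2 the checks that bear on exposure coding only move the cut.
- The person-level random effect in 5.2 was not modelled in this check.

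**Conclusion.** The point holds for SAP 5.2. The section should state its calendar-time adjustment, and once that is included the greater-than-6-month coefficient cannot be read as the average effect after 6 months unless the effect is flat from then on. With Period 0, the weight on the longest exposure is negative throughout the assumed range, but it can be as small as -0.09. Without Period 0, as in the main analysis, it is larger: -0.51 on months 21-27 of the delivered layout at autocorrelation 1. Lower autocorrelation brings it closer to zero.

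For TEC the conclusion is narrower: the late effect mainly describes months 6-12 (weight 0.84 to 1.01 for ICC 0.01-0.2).

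The weights rest on a facility random intercept, categorical period effects and the assumed ICC and autocorrelation. They show what the plan cannot detect, not that a reported result is biased. Both outcomes are secondary. The primary outcome compares Wave 1 with Wave 4 and is unaffected.

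**What to change.** In SAP 5.2:
1. Add categorical calendar-period terms to the model.
2. Pre-specify exposure bands of 0-6, 6-12, 12-18 and over 18 months, and report each. On the delivered calendar, split the last band at month 21, when Wave 4 crosses.
3. Report an equally weighted late average, each month of exposure counting the same, over the bands observed while control clinics remain. Show it next to the two-level result.

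In SAP 4.0, state that the late TEC effect mainly reflects months 6-12, or fit separate 6-12 and over-12 bands.

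The cost is SAP wording, a rerun and some precision. In 5.2 the standard error of that late average is about 9% above that of the pooled late term with Period 0, and about 30% (delivered layout) to 37% (planned layout) above it without, at autocorrelation 1. Extending the average to months 18-24, where no controls remain, costs more: 0.27 against 0.21 points on the planned layout with Period 0. In TEC the standard error rises from about 7.1 to 8.2 points at ICC 0.2 if both late bands are averaged.

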With first diagnosed case of COVID-19 in Zambia on the 18th of March 2020, the context of the implementation of the PCC intervention has changed dramatically. As the COVID-19 pandemic progresses globally and in Zambia, the situation in which HIV care is delivered will be dynamic. Initial responses included the Ministry of Health issuing a directive on 24th March 2020 to dispense a 6-month antiretroviral therapy (ART) supply to all patients on HIV treatment, and all sites began a process of calling patients into the clinic, regardless of the timing of their last visit. In accordance with guidance from CDC and PEPFAR, community-based activities such as testing campaigns have been suspended; and resources redirected to surveillance and testing for COVID-19. Health facilities have implemented measures including screening of patients of symptoms upon arrival, triage of suspected COVID-19-positive patients, maintaining a distance of 1 metre or more between patients who are waiting to be attended to and installing additional handwashing stations. Just as the context has changed, the experience of patients and providers has changed. To understand HIV care delivery – critical and life-saving services that must continue under any circumstances – we will assess the patient and provider experiences under these conditions, leveraging the study platforms established for prior measurements.

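### The missed-next-visit model in SAP 5.2 names no period or calendar-time term, so the stepped-wedge estimate as written is open to confounding by secular trend

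*Combined protocol and SAP*

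**What the plan says.** SAP 5.2 describes the model in one paragraph.

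- **Structure:** "We will use mixed effects logistic regression, accounting for clustering at both the individual- and the facility-level using random effects".
- **Exposure:** assigned visit by visit. Because a lag is expected, "we will code intervention periods as control, early intervention" (up to 6 months) and late intervention (beyond 6 months).
- **Data:** "The 6-month period prior to study start will be included as a Period 0 when all facilities are control".
- **Adjustment:** "care status at enrollment (in care, new ART, LTFU), sex, age, time in care, baseline clinic-level retention", and "randomization strata (initial cluster randomization stratified by facility size and viral load coverage based on programmatic data").
- **Optional terms:** "potential confounders due to imbalance in randomization: WHO severity groups, marital status, and education".
- **Sensitivity analyses:** a 90-day threshold, and a 3- or 9-month lag.

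None of these is a calendar-time term. The TEC model in SAP 4.0 differs: there, "period is included as a fixed categorical variable to adjust for secular trends", with splines as alternatives and visit date as a sensitivity analysis. Section 5.2 does not refer back to it. Protocol 8.8 does not fill the gap, since its retention analysis (Kaplan-Meier, log-rank, Cox) has no period term either.

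**The concern.** In a stepped wedge, exposure rises with calendar time by design. An effect estimated without a time term absorbs any change in the outcome that would have happened anyway.

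Here the documents describe such changes. Figure S1 says Period 2 began in February 2020 and was extended because of COVID-19. Protocol 5.1 (Objective 1) reports a directive of 24 March 2020 "to dispense a 6-month antiretroviral therapy (ART) supply to all patients on HIV treatment", with sites calling patients in whatever the date of their last visit. The Figure S6 legend says appointment intervals lengthened greatly. Each could alter the chance of being more than 30 days late for the next visit, at control and intervention facilities alike.

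Nothing listed in 5.2 substitutes for period. Time in care is patient tenure, baseline clinic retention is one pre-study value per clinic, Period 0 is added data, and early/late is time since crossover.

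**Working it through.** **1. Planned visits (SAP 5.2 table).** Waves 1 to 4 contribute 60,000, 30,000, 30,000 and 60,000 visits per period. (60,000 + 30,000 + 30,000 + 60,000) × 5 = 900,000, which reproduces the stated total.

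**2. How exposure follows time.**

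| Period | Control | Early | Late | Intervention share |
|---|---|---|---|---|
| 0 | 180,000 | 0 | 0 | 0% |
| 1 | 120,000 | 60,000 | 0 | 33% |
| 2 | 90,000 | 30,000 | 60,000 | 50% |
| 3 | 60,000 | 30,000 | 90,000 | 67% |
| 4 | 0 | 60,000 | 120,000 | 100% |

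Visits in Period 2 or later are 150,000/450,000 = 33% of control, 120,000/180,000 = 67% of early and 270,000/270,000 = 100% of late visits.

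**3. Expected estimate under no true effect, no period term.** I use a linear approximation on facility-period means, equal periods and a trend common to all facilities. Each facility-period has 60,000/8 = 30,000/4 = 7,500 visits. With that many, a facility random intercept behaves almost as a fixed one, so the calculation can be done within facility.

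A facility in waves 1, 2, 3, 4 has one early period each and 3, 2, 1, 0 late periods out of five. Summing over 8, 4, 4, 8 facilities after centring within facility:

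- S_EE = 24 × (1 − 1/5) = 19.2
- S_LL = 8(1.2) + 4(1.2) + 4(0.8) = 17.6
- S_EL = −[8(0.6) + 4(0.4) + 4(0.2)] = −7.2
- Determinant = 19.2 × 17.6 − 7.2² = 286.08

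Then b_E = (17.6 S_Ey + 7.2 S_Ly)/286.08 and b_L = (19.2 S_Ly + 7.2 S_Ey)/286.08.

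| Trend in Periods 0–4 (points) | S_Ey | S_Ly | False early | False late |
|---|---|---|---|---|
| Step from Period 2: 0,0,1,1,1 | 1.6 | 14.4 | 131.84/286.08 = 0.46 | 288/286.08 = 1.01 |
| Linear: 0,1,2,3,4 | 12 | 44 | 528/286.08 = 1.85 | 931.2/286.08 = 3.26 |
| Period 2 only: 0,0,1,0,0 | −0.8 | 0.8 | −8.32/286.08 = −0.03 | 9.6/286.08 = 0.03 |

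Generalized least squares with a facility random intercept and an assumed intraclass correlation of 0.01 to 0.2 gives 0.46 and 1.01, 1.84–1.85 and 3.25–3.26, and −0.03 and 0.03. Signs reverse if the trend falls.

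**4. With period as a categorical fixed effect**, a trend common to all facilities is absorbed. Both estimates are 0.00 in every case.

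**5. Without Period 0.** The Table S13 footnote says the main report dropped it. The same least-squares calculation on Periods 1 to 4 gives about 0.36 and 0.94 (step), 1.5 and 3.1 (linear), and −0.23 and −0.23 (Period 2 only).

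**6. Scale.** Table S13 reports −2.0 (95% CI −2.3 to −1.7) early and −3.7 (−4.1 to −3.4) late. A sustained 1-point shift exceeds the half-width of either interval in the late estimate.

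**The case against.** The best defence is that the list in 5.2 is introduced as adjustment for baseline imbalance and for precision, so a design term need not appear in it. The paragraph says it uses the full stepped-wedge design, cites stepped-wedge methods papers, and sits in a SAP whose section 4.0 treats fixed period as standard. That makes an unstated intention plausible. But those citations support the lag coding, the random effects and exposure coding are spelled out, and the clause on alternate specifications covers only convergence and overfitting. Someone following 5.2 literally would fit no time term.

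The Figure S6 legend also records that the outcome was changed from time-to-event to next visit because of COVID-19. That reduces sensitivity to appointment length but does not adjust for secular trend.

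Three stronger readings are tempting, and the documents do not support them.

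- **That Table S13 measures the bias.** Crude differences are 22.6 − 22.1 = +0.5 and 21.5 − 22.1 = −0.6, against adjusted −2.0 and −3.7. But covariates that 5.2 does list also move these figures. Arm sizes back-calculated from Table S13 (count divided by rounded percentage; control returners by subtraction, 130,035 − 8,318 − 99,808 = 21,909) put returners at about 12.0%, 16.1% and 20.8% of control, early and late visits. Applying control rates (28.5% new ART, 20.5% in care, 31.2% returner) to each arm's mix gives expected 22.68% early and 23.23% late. Observed minus expected is 22.62 − 22.68 = −0.06 and 21.49 − 23.23 = −1.74. Care status alone removes the positive early difference. The rest is not attributed anywhere.
- **That COVID-19 produced the reported benefit, or that the fitted model lacked period.** Neither is shown. If time adjustment did explain the crude-to-adjusted gap, the fitted model contained a time term, and omitting it would have hidden benefit.
- **That this is essentially a before-after comparison.** Periods 1 to 3 have concurrent arms and hold 3 × 180,000 = 540,000 of 900,000 planned visits.

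**Conclusion.** The point stands as a defect in the written plan. SAP 5.2 sets out exposure, random effects and covariates for a stepped-wedge analysis and names no adjustment for calendar time, in a trial whose control and intervention visits are unequally spread across a documented system-wide disruption.

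Direction and size are unknown because the documents give no secular trend for this outcome. The range above, from about 0.03 points for a Period 2-only disturbance to about 1.8 and 3.3 points for a 1-point-per-period trend, rests on illustrative 1-point trends common to all facilities, equal periods, planned visit counts, a linear approximation and an assumed intraclass correlation. It shows how the omission would act, not what happened in the reported results.

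The outcome is secondary. The primary outcome compares waves 1 and 4 in parallel and is not affected. I would class this as should-fix.

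**What to change.** In SAP 5.2, state that period (0 to 4, or 1 to 4 where Period 0 is left out) enters as a categorical fixed effect, and that the same term is used in the subgroup and 90-day models. Add calendar month or visit date as a sensitivity analysis, because Period 2 lasted nine months (Figure S1) and a single period effect may not capture change within it.

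State with the results whether the reported missed-visit models included period. If they did, the change is one sentence of documentation. If not, the models should be refitted. The cost is one categorical term and somewhat wider confidence intervals; no new data are needed.
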